# A randomised trial of treating fibroids with either embolisation or myomectomy to measure the effect on quality of life among women wishing to avoid hysterectomy (the FEMME study): study protocol for a randomised controlled trial

**DOI:** 10.1186/1745-6215-15-468

**Published:** 2014-11-29

**Keywords:** Uterine fibroids, UAE, Myomectomy, Quality of life, Menstrual blood loss, Ovarian reserve

## Abstract

**Background:**

Uterine fibroids are the most common tumour in women of reproductive age. By the time they are 50-years-old around 80% of women will have developed one. Of these, around half will experience symptoms which will impact negatively on their quality of life. Hysterectomy is the traditional treatment for women with symptomatic fibroids. For women who do not wish to undergo a hysterectomy, two invasive treatments are commonly available: myomectomy or uterine artery embolization (UAE).

**Design:**

FEMME is a pragmatic, randomised, open, multi-centre trial examining the quality of life menstruating women with symptomatic fibroids experience after treatment with UAE or myomectomy.

**Methods:**

After providing informed consent, 216 women with symptomatic fibroids from 43 NHS Hospital Trusts and Health Boards across the United Kingdom will undergo randomisation by a centralised computer system to treatment by either UAE or myomectomy. A minimisation algorithm will be used in order to balance the groups with respect to the following three parameters: the longest dimension of the largest fibroid, the number of fibroids present, and whether the woman currently desires pregnancy.

Using validated questionnaires the women’s quality of life will be compared between groups at six months, one year, two years and four years post-procedure, taking into account pre-procedure scores. An economic evaluation will be conducted alongside the trial to determine the cost-effectiveness of UAE compared with myomectomy.

Validated diaries will also be used to compare menstrual blood loss at the same time-points. The plasma concentration of Anti-Müllerian hormone (AMH), which will act as a proxy measurement of ovarian reserve, will be recorded before the woman has her procedure and then again at six weeks, six months, and twelve months afterwards. Re-intervention rates will be recorded.

**Discussion:**

The FEMME trial’s primary outcome is the quality of life women with symptomatic uterine fibroids experience two years after they have been treated with either UAE or myomectomy, as measured by the disease-specific Uterine Fibroid Symptom Quality-of-Life (UFS-QoL) questionnaire.

**Trial registration:**

Current Controlled Trials registration number: ISRCTN70772394, registered on 2 March 2013.

## Background

### Why is there a need to determine whether treatment with uterine artery embolisation or myomectomy is most efficacious in improving the quality of life of women with uterine fibroids?

Uterine fibroids are the most common tumour in women of reproductive age and increase in prevalence as the woman gets older. By the time they are 50-years-old, around 80% of women will have developed a fibroid. Approximately half of women with fibroids experience significant symptoms which can include heavy menstrual bleeding (HMB), pain on intercourse, abdominal pain, and a feeling of pressure, all of which can impact significantly on the woman’s quality of life [1].

The symptoms experienced by the woman with fibroids may vary depending on the position, size and number of fibroids. Intramural fibroids are the most common form of fibroid but are frequently asymptomatic. Subserosal fibroids, located on the outer surface of the uterus, can become very large and create feelings of bulkiness. Submucosal fibroids project into the uterine cavity and are associated with HMB. As they may distort the uterus and change the local morphology of the uterine tissue, some clinicians believe that the presence of fibroids may have a negative impact on fertility [2]. The Hospital Episode Statistics state that there were just under 31,000 Finished Consultant Episodes of women with fibroids of the uterus between 2012 and 2013 in the United Kingdom. The majority of these women were aged between 40 and 54-years-old [3].

Women with symptomatic fibroids often respond poorly to drug management or risk unacceptable side effects from hormonal preparations [4], so generally the use of these pharmaceuticals is limited to reducing the fibroid bulk and relieving the symptoms prior to surgical intervention. The traditional treatment for symptomatic fibroids is hysterectomy, but with many women associating their uterus with their femininity and sexuality, an increasing number of women with fibroids are questioning whether hysterectomy for a benign condition is necessary and many are seeking alternatives.

In the National Health Service (NHS) there are two womb-sparing procedures available to treat uterine fibroids; uterine artery embolisation (UAE) and myomectomy. In UAE, an arterial catheter is used to introduce an embolic agent into the blood vessel supplying the uterus. This blocks the blood flow to the fibroid causing it to infarct (die), so relieving the symptoms of the fibroid. Myomectomy is the surgical removal of the fibroid, and depending on the size and position of the fibroid, this can be undertaken by a variety of routes including laparoscopic, hysteroscopic, or by a laparotomy.

### Previous work comparing UAE with myomectomy

The use of UAE in women who may wish to conceive is controversial within some sections of the medical community. Some authors are concerned by the reduction in blood flow to the ovary that can occur if there are significant connections between the ovarian and uterine arteries, which may result in decreased ovarian function [5]. The extent of this decreased function, how long it is maintained for, and even if it occurs at all, is disputed [6, 7]. Whilst generally regarded as safe [8], the caution inherent in the guidelines drawn up when UAE was still in its infancy has led to a further reluctance in some circles to use UAE in women who may wish to try to conceive at some point. As a result of this, trials generally excluded women who are seeking fertility.

One small (n = 121) single centre, randomised, clinical trial from the Czech Republic compared myomectomy with UAE in women with intramural fibroids [9]. These authors concluded that UAE was less invasive, but as effective and safe as myomectomy for treating the symptoms of fibroids. The REST trial [10] randomised a total of 157 women in a 2:1 ratio between UAE and myomectomy before assessing the quality of life (QoL) at five years with the Short Form 36 (SF-36) general health survey. Secondary measures included complications, adverse events, and the need for further intervention. These authors reported that there were no significant differences in the reported QoL between the groups at five years. However, there was a significantly greater re-intervention rate after five years for treatment failure or complications in the UAE arm over the myomectomy arm. This negated the initial cost benefit of UAE over surgery at 12 months and made both treatments cost-neutral at five years [10].

A pilot study for the FEMME trial (the FUME study [11]) was conducted at St George’s Hospital, London, United Kingdom. In this study 160 women with symptomatic uterine fibroids were randomised to UAE or myomectomy and the change in their QoL, hospital stay, complication rates, and need for re-intervention were measured at one year post-procedure. The authors reported that by one year there was no difference in the improvement of the QoL women experienced in the myomectomy and UAE arm but, like the REST trial, there was a higher intervention rate in women who had undergone a UAE [11].

With increasing pressure on ever diminishing NHS budgets the cost-effectiveness is increasing in importance to commissioners and Trusts when deciding which treatment options should be available. The average length of stay in hospital post-hysterectomy is 4.4 days [10], and it is not unusual for women to require an additional three months to recuperate before returning to their normal lives. The average stay in hospital post-myomectomy is 3.6 days and, depending on the route used, the post-procedure recuperation time can be up to several weeks. With its minimally invasive nature, the mean length of hospital stay post-UAE is one day, with a return to normal life typically within a couple of weeks. Whilst superficially this may suggest a significant economic advantage for UAE, the higher re-intervention rates compared with hysterectomy may well negate any cost saving by five years [10].

## Methods/Design

### Study design

The FEMME trial is a randomised, open, multi-centre trial comparing UAE with myomectomy in women with symptomatic uterine fibroids.

### Primary outcome

The FEMME trial’s primary outcome is to measure the QoL women with symptomatic uterine fibroids experience two years after they have been treated with UAE or myomectomy, through the disease-specific Uterine Fibroid Symptom Quality of Life (UFS-QoL) questionnaire.

### Secondary outcomes

The FEMME trial’s secondary outcomes are:EuroQoL EQ-5D score and visual analogue scale score;Menstrual blood loss, assessed using the Pictorial Blood loss Assessment Chart (PBAC). This is a validated and well-used assessment of menstrual blood loss in women with uterine fibroids;Pregnancy outcomes - pregnancy will be reported by the woman in the first instance. The research nurse or trial coordinator will collect further information with respect to timing of pregnancy, biochemical pregnancy (positive pregnancy test), incidence of miscarriage, outcome of pregnancy, gestational age at delivery or miscarriage, complications of pregnancy, and labour;Adverse events - all adverse outcomes considered to be related to the study protocol or intervention will be collected. Since adverse outcomes may occur many months after intervention, these data will continue to be collected throughout the study;Length of hospital stay;Time to return to work or usual activity;Further treatment for incomplete removal or recurrence of symptoms, including hysterectomies;Ovarian reserve - blood samples will be taken from the women in each treatment arm for the measurement of the plasma levels of Anti-Müllerian hormone (AMH), a compound used as a proxy measurement of ovarian reserve, to determine if there is any difference at six weeks, six months, and twelve months post-procedure.

The time-points at which these follow-ups are performed are shown in Table 1.

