**Table 1 Tab1:** **Time-points at which outcomes are recorded**

Outcome measure	Prior to randomisation	Before discharge	6 weeks	6 months	1 year	2 years	4 years
UFS-QoL/EQ-5D	×			×	×	×	×
Pregnancy				×	×	×	×
Outcomes of pregnancy					As reported by participant		
PBAC	×			×	×	×	×
Fertility potential	×		×	×	×		
Resource usage (clinical)	×	×		×			
Technical success				×			
Serious adverse events					As reported by clinician/participant		
Further treatment				×	×	×	×

Legend:

UFS-QoL: Uterine Fibroid Symptoms – Quality of Life.

EQ-5D: EuroQol – 5D score and visual analogue scale score.

PBAC - the Pictorial Blood loss Assessment Chart.

With an increasing number of women seeking an alternative to hysterectomy, this timely trial will investigate the role of UAE and myomectomy in treating women with symptomatic uterine fibroids, and so inform women as to the most appropriate treatment for them.

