### Treatment

A pregnancy test will be performed immediately prior to treatment. As FEMME is a pragmatic trial, other than the randomisation to myomectomy or UAE the treatment the woman receives is the clinician’s normal practice. This means that if the woman is randomised to a myomectomy this can be of any type including laparoscopic, hysteroscopic, or by a laparotomy. Similarly, should the woman be randomised to UAE, this is performed according to the interventional radiologist’s normal practice. Information collected at the time of the procedure will include details of the treatment received, any adverse events experienced by the participant, and the length of in-patient stay.

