#### Monitoring of all types of adverse event

All types of adverse event which occur to participants in the FEMME trial will be reported as soon as possible after the clinician becomes aware of the event. An adverse events form should be completed as fully as possible and sent via fax to the trials office. This form will include an assessment of causality. Upon receipt, the trials office will log details of the adverse event on that patient’s record on the central trials database and forward an anonymised copy of the form to the sponsor and the Chief Investigator. Anonymised details of all adverse events will be presented to the DMC for scrutiny each time they meet. These anonymised details will be reported to the REC annually.

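### The adverse-event outcome is limited to events judged related, while the monitoring section has all events reported; in an open trial the two rules need to be reconciled

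*Protocol article*

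**What the plan says.** The protocol article sets the scope of adverse events in several places.

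- **Secondary outcomes.** The outcome is introduced with the statement that "all adverse outcomes considered to be related to the study protocol or intervention will be collected". Collection is open-ended in time: "Since adverse outcomes may occur many months after intervention, these data will continue to be collected throughout the study". The section closes by sending the reader to the schedule: "The time-points at which these follow-ups are performed are shown in Table 1".
- **Table 1.** The only adverse-event row is labelled "Serious adverse events". It has no fixed visit; events are entered when a clinician or participant reports them. No row covers non-serious events.
- **Treatment.** Information gathered at the procedure includes "any adverse events experienced by the participant", with no condition on relatedness or seriousness.
- **Monitoring of all types of adverse event.** Here the rule for sites is wider: "All types of adverse event which occur to participants in the FEMME trial will be reported as soon as possible". On the report form: "This form will include an assessment of causality". The same section says that anonymised details of all adverse events go to the DMC.
- **Data Monitoring Committee.** The committee's reports cover any adverse events that participants suffer, again without a relatedness condition.

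On blinding, Study design states: "The FEMME trial is a randomised, open, multi-centre trial comparing UAE with myomectomy in women with symptomatic uterine fibroids".

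**The concern.** The outcome definition and the monitoring section give causality different jobs. In the first, being considered related is the condition for an event to be collected. In the second, every event is reported and causality is one item on the form. An event thought unrelated is outside the first rule and inside the second.

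This matters because of the design. The clinician who judges relatedness knows the treatment, and the arms are a surgical and a radiological procedure, so the same later event could be attributed differently in each. The article itself expects some adverse outcomes many months after the intervention, when attribution is hardest. More than 40 centres have to apply the rule, so different readings are possible. If some sites used relatedness as a filter, events could be missing from the safety comparison in a way that depends on arm, and no later analysis could recover events that were never sent.

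**Working it through.** The article states no adverse-event rate, margin or power for safety, so there is no figure of the plan to reproduce. The check is a comparison of the text.

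**Step 1: scope by section.**

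| Section | Restricted to related? | Restricted to serious? | What the section governs |
|---|---|---|---|
| Secondary outcomes | Yes | No | Outcome definition, worded as a rule on collection |
| Table 1 | No | Yes, by row label | Timing |
| Treatment | No | No | Collection at the procedure |
| Monitoring of all types of adverse event | No | No | Reporting to the trials office |
| Data Monitoring Committee | No | No | Content of reports to the committee |

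**Step 2: which conflicts are firm.** Secondary outcomes against the monitoring section is firm. Both say what is gathered, and they give different answers for an event judged unrelated. Table 1 is weaker: its title concerns time-points, and it is not exhaustive, since hospital stay and return to work are secondary outcomes with no row of their own name. It still adds to the ambiguity, because Secondary outcomes refers to it for timing and it names no other class of adverse event.

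**Step 3: what follows under each reading.**

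- *All sites follow the monitoring section.* All events are in the database with a causality field, and an all-event comparison is possible. Only the outcome as worded under Secondary outcomes is filtered by relatedness.
- *Some or all sites follow Secondary outcomes.* Events judged unrelated may not be sent. The filter then acts on the data themselves, through a judgement made with knowledge of treatment.

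**Step 4: scale, on assumed inputs only.** Let p be the true risk, equal in both arms, and let r₁ and r₂ be the proportions of events judged related. The observed risks are p·r₁ and p·r₂, and the apparent relative risk is r₁/r₂ whatever p is. Take 216/2 = 108 women per arm, a two-sided 5% test, p from 20% to 40%, and r₁ = 0.90:

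| r₂ | Observed risks at p = 20% | Apparent relative risk | Chance of a false significant difference, p = 20% to 40% |
|---|---|---|---|
| 0.70 | 0.20 × 0.90 = 0.18; 0.20 × 0.70 = 0.14 | 0.18/0.14 = 1.29 | about 12% to 24% |
| 0.60 | 0.18; 0.20 × 0.60 = 0.12 | 0.18/0.12 = 1.50 | about 23% to 49% |
| 0.50 | 0.18; 0.20 × 0.50 = 0.10 | 0.18/0.10 = 1.80 | about 40% to 75% |

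If r₁ = r₂, or if all events are counted, the relative risk is 1 and the error rate stays near 5%. Swapping the arms inverts the ratios (0.14/0.18 = 0.78 for the first row). None of p, r₁ or r₂ comes from the article. The table shows only that the result depends entirely on differential attribution, about which the article gives no information.

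**The case against.** The strongest reply is that the passages can be read together: Secondary outcomes lists what will be analysed, the monitoring section describes what will be reported, and an outcome of related events drawn from a full database with a causality field is coherent. Treatment-related complications are also a legitimate outcome. This has weight, and it is why bias is not shown. It does not remove the conflict, because Secondary outcomes says related events are what will be collected, and nothing in the article confines that to analysis.

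Three stronger readings are tempting, and the article does not support them.

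- *The protocol creates three separate datasets.* A reader might infer this from the three labels. Table 1 is a timing table and not exhaustive, so its row label is not a firm third scope.
- *The DMC cannot see unexpected harms.* The monitoring and DMC sections both promise it all events. The gap would arise only at sites that put the outcome definition ahead of those sections.
- *The safety comparison is biased by some known amount.* Differential attribution between the two procedures is plausible in an open trial, but the article neither states nor quantifies it.

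It is also fair to say that several consequences of treatment are captured with no causality filter: further treatment including hysterectomy, hospital stay, and additional procedures and admissions under Follow-up. These limit what could be lost but do not replace an adverse-event comparison.

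Finally, the article condenses a fuller protocol, which may define these terms in detail and was not available for this check, and neither was the SAP. That would excuse missing detail, but here the article's own statements disagree.

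**Conclusion.** The point holds as an unreconciled contradiction. The outcome definition makes relatedness a condition of collection, while the monitoring section, supported by the treatment and DMC sections, does not. Because the trial is open and no blinded causality assessment is described, the narrower rule would let a judgement made with knowledge of treatment decide whether an event counts in the comparison between arms.

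The reach depends on site practice. At the least, only the outcome as defined is filtered and a complete database remains. At the most, events are missing from the data. The article does not show which applies, and the size and direction of any bias cannot be computed from it. The point concerns one secondary outcome and leaves the primary quality-of-life comparison untouched. It should be corrected, because the safety comparison bears on the choice between the procedures and the remedy is cheap.

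**What to change.** Reconcile the sections on the rule that the monitoring section already states:

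1. Amend the adverse-event entry under Secondary outcomes so that all adverse events are collected regardless of causality, with seriousness and causality recorded as attributes of each event.
2. Relabel the Table 1 row to cover all adverse events, with serious events identified within it.
3. Report the comparison between arms for all events, alongside the related and serious subsets. Related complications then remain visible without being the only view. Which of these leads the presentation is partly a matter of preference; what matters is that the all-event result is shown.
4. Remind sites of the single rule. The article describes the trial as still recruiting, so this could protect data yet to be gathered.

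The cost is a wording amendment, a message to sites, and some extra form-filling wherever the narrower rule was applied. With 216 women followed for up to four years at more than 40 centres, that extra work is not nil, but it is no more than the monitoring section already asks for.

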**Table 1 Tab1:** **Time-points at which outcomes are recorded**

Outcome measure	Prior to randomisation	Before discharge	6 weeks	6 months	1 year	2 years	4 years
UFS-QoL/EQ-5D	×			×	×	×	×
Pregnancy				×	×	×	×
Outcomes of pregnancy					As reported by participant		
PBAC	×			×	×	×	×
Fertility potential	×		×	×	×		
Resource usage (clinical)	×	×		×			
Technical success				×			
Serious adverse events					As reported by clinician/participant		
Further treatment				×	×	×	×

Legend:

UFS-QoL: Uterine Fibroid Symptoms – Quality of Life.

EQ-5D: EuroQol – 5D score and visual analogue scale score.

PBAC - the Pictorial Blood loss Assessment Chart.

With an increasing number of women seeking an alternative to hysterectomy, this timely trial will investigate the role of UAE and myomectomy in treating women with symptomatic uterine fibroids, and so inform women as to the most appropriate treatment for them.

### Recruitment

Patients will be recruited from multiple (more than 40) secondary and tertiary centres throughout the United Kingdom, including specialist centres, district general, and large teaching hospitals. Centres will be able to participate in the FEMME trial if a care pathway is present which allows eligible women presenting at the site to be randomised between UAE and myomectomy.

### Eligibility criteria

A woman is eligible to be considered to take part in the FEMME trial if:They have menstruated within the preceding twelve months and present with symptomatic fibroids which the reviewing clinician feels can be treated equally well with UAE or myomectomy;The woman has not undergone a previous myomectomy via a laparotomy or a previous UAE;They are over 18 years of age, not pregnant, and are prepared to accept a hysterectomy in an emergency;There is no evidence of malignancy, pelvic inflammatory disease, or significant (in the opinion of the reviewing clinician) adenomyosis.Full eligibility criteria are shown in Figure 1.

